### Concealment mechanism {16b}

Randomization will be performed by an independent data manager who is not involved in the study.

The document describing the allocation sequence is not accessible for researchers involved in the study. Only the data manager has access to this document.

### Implementation {16c}

The data manager will generate the allocation sequence. The data manager will inform the researcher of the allocated group to which the participant is randomized. Subsequently, the researcher will inform the participant by telephone and will explain the next steps of the study.

## Assignment of interventions: blinding

### Who will be blinded {17a}

This is an open-label study. Due to the nature of the intervention (ICBT) and the control condition (care as usual), blinding is not required or possible.

### Procedure for unblinding if needed {17b}

Blinding will not occur (see previous point).

## Data collection and management

### Plans for assessment and collection of outcomes {18a}

Participants complete a set of online questionnaires at home. The first assessment is at baseline, the second at 6-month follow-up (i.e., post-treatment for the intervention group) being the primary outcome measure for the analyses, and the third and last assessment is at 12-month follow-up (i.e., 6 months post-treatment for the intervention group). See Table 1 for an overview of the specific questionnaires for each assessment and Fig. 1 for the participant timeline.

### Plans to promote participant retention and complete follow-up {18b}

The assessments consist of online questionnaires that participants can complete at home, at a moment that suits them. To split up completion time, participants can pause the questionnaires at any moment and continue completion within the next 14 days. To promote participant retention in the intervention condition, we will tailor the treatment to the participant’s wishes, needs, and abilities. In addition, the e-Coaches will regularly ask patients for feedback to make adjustments if necessary. This could mean, for example, that for a given patient treatment will include less psychoeducational texts, more practical exercises, and additional phone calls with the e-Coach therapist.

### Data management {19}

Participant identification codes will be used to link data to participants. The file containing the linking between participant numbers and personal data (e.g., name, date of birth) will be managed by the researchers and will be locked for access by others. All the information collected in this trial will be stored in a secured locker. Electronic data will be stored on the central server of the Health, Medical, and Neuropsychology unit of Leiden University, which will be backed up daily. Collected data (personal data from informed consents and medical files, self-report data from questionnaires) will be stored for a period of 15 years.

### Confidentiality {27}

Participant identification codes will be used to link data to participants. The file containing the linking between participant numbers and personal data (e.g., name, date of birth) will be managed by the researchers and will be locked for access by others.

### Plans for collection, laboratory evaluation, and storage of biological specimens for genetic or molecular analysis in this trial/future use {33}

Not applicable, this trial does not have biological specimens.

## Statistical methods

### Statistical methods for primary and secondary outcomes {20a}

Descriptive statistics (means, standard deviations, medians, and interquartile ranges) of relevant variables will be calculated. In case of non-normally distributed variables, transformations will be applied to allow parametric statistics. Baseline data of the intervention and control condition will be compared to assess similarity. Additionally, several *t*-tests will be performed on the 6-month follow-up data, both on the primary and secondary outcomes.

To examine differences in the primary outcome measure change in distress between patients in the intervention and control condition, a linear mixed-model analysis of variance will be conducted. Linear mixed-effects modeling has superior qualities with regard to missing values and makes use of all available data, making this a full-intention-to-treat analysis. Models will be fitted with full information maximum likelihood estimation. Between-group effects at post-treatment and follow-up will be analyzed with baseline scores of dependent variables as covariates. Time will be operationalized as a continuous variable, because post-treatment assessment will vary across participants as a result of different intervention length. Fixed linear effects of time and condition will be included and random effects of intercept.

Similar mixed-model analyses of variance will be conducted to examine differences in change in the scores on the secondary outcome measurements between the two conditions. In addition, correlational and regression analyses will be performed to assess the potential role of demographic and clinical characteristics and psychological parameters (e.g., treatment expectancies, therapeutic relationship) on the effects of the ICBT intervention.

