### Sample size {14}

The power calculation is based on the difference in change of distress from baseline to follow-up between the intervention and the control group. The effect size was based on previous RCTs on (Internet-based) CBT treatment in dialysis patients with a focus on distress-related outcomes (e.g., depression) indicating medium effects [73, 74]. In the absence of studies focusing on a broader spectrum of adjustment problems such as the current study, we used these studies for an estimation of the effect size despite the fact that they focused solely on distress. When using an alpha level of .05 and an effect size of 0.50 (Cohen’s *d* moderate effect), and taking account of potential dropouts, effects for 2 groups of 65 patients yield a power of at least .80.

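### Maximum likelihood with only a random intercept slightly understates the standard error, and mis-sizes a 6-month contrast if the two follow-up variances differ

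*Protocol article*

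**What the plan says.** All of the model wording is in the protocol article, Statistical methods for primary and secondary outcomes {20a}.

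- Estimator: "Models will be fitted with full information maximum likelihood estimation".
- Fixed and random terms: "Fixed linear effects of time and condition will be included and random effects of intercept". No time-by-condition term, visit-specific variance or degrees-of-freedom method is named.
- Baseline: "Between-group effects at post-treatment and follow-up will be analyzed with baseline scores of dependent variables as covariates". The modelled responses are therefore the 6- and 12-month scores, two per patient.
- Time: "Time will be operationalized as a continuous variable, because post-treatment assessment will vary across participants as a result of different intervention length".
- Related analyses: secondary outcomes get similar mixed models, and t-tests on the 6-month data are planned in addition.

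Plans for assessment and collection of outcomes {18a} sets the primary time point: "the second at 6-month follow-up (i.e., post-treatment for the intervention group) being the primary outcome measure for the analyses". Sample size {14} sets the error rate and effect: "When using an alpha level of .05 and an effect size of 0.50", with 65 patients per group and power of at least .80.

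**The concern.** Two separate features of the stated model affect the SE of the treatment effect.

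**Estimator.** Maximum likelihood does not correct the variance estimate for the fixed effects that have been fitted. The variance, and with it the SE, is biased low. The direction is always the same: intervals a little too narrow and p-values a little too small.

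**Covariance.** With two responses per patient, a random intercept leaves their (positive) correlation free but constrains their variances to be equal. An effect estimated at 6 months then borrows its variance from both visits. If distress is more variable at 6 months than at 12, the SE is too small and false positives rise. If it is more variable at 12 months, the SE is too large and power is lost. Therapy lasts 3 to 4 months, so one visit falls fairly soon after it ends and the other much later. Nothing in the plan supports equal spread at the two.

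At stake are the coverage of the interval and the size of the test for the primary outcome. The same wording carries over to the secondary outcomes.

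**Working it through.** **Inputs from the document.** 65 per arm (n = 130), d = 0.50, alpha .05, fixed effects of time, condition and baseline, random intercept, primary time point 6 months.

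**Assumptions, not in the document.** Two-sided test; n = 104 to represent 20% loss (130 x 0.8); 12/6-month residual variance ratio r of 0.6 to 1.6; d expressed in units of the 6-month residual SD. The simulations also assume a baseline correlation of 0.5, a 6-12 month correlation of 0.6 and dropout of 0-15% per visit.

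**1. The plan's own power.** Noncentrality = 0.5 x sqrt(65/2) = 2.850. Normal approximation: Phi(2.850 - 1.960) = 0.813; noncentral t: 0.808. The stated .80 is reproduced if all 65 per arm are analysed. The number needed is 2 x (1.960 + 0.842)^2 / 0.25 = 62.8, so 63 per arm. There is little power to spare.

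**2. Maximum likelihood alone.** For the condition effect with complete pairs, three patient-level terms count (intercept, condition, baseline). The SE ratio to REML is sqrt((n - 3)/n). The true size is 2 x P(t with n - 3 df > c x ratio), where c is the critical value used.

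| n | SE ratio | size, c = 1.96 | size, c from t |
|---|---|---|---|
| 130 | 0.988 | 5.5% | 5.3% |
| 104 | 0.986 | 5.6% | 5.3% |

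**3. The 6-month contrast under a random intercept.** This contrast needs a time-by-condition term. The model's variance at 6 months is close to the average of the two visit variances. The SE is therefore off by sqrt((1 + r)/2), which does not depend on the within-patient correlation. Multiplying by the maximum-likelihood factor from step 2, with c = 1.96:

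| r (12/6-month variance) | sqrt((1 + r)/2) | size, n = 104 | power, n = 130, d = 0.50 |
|---|---|---|---|
| 0.6 | 0.894 | 8.7% | not comparable, size inflated |
| 0.7 | 0.922 | 7.8% | not comparable, size inflated |
| 1.0 | 1.000 | 5.6% | 0.82 |
| 1.3 | 1.072 | 4.1% | 0.78 |
| 1.6 | 1.140 | 3.0% | 0.74 |

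With the 6-month variance estimated on its own and a t reference, power at n = 130 is 0.81. Simulation of the two-visit model at n = 104 gave sizes of 7.5-8.4% for r of 0.6-0.7 and 2.7-4.0% for r of 1.3-1.6, in line with the closed form.

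**4. The listed terms taken literally, with one condition effect pooled over both visits.** In 4,000-run null simulations (Monte Carlo error about 0.35 points), with SD ratios up to 1.5 in either direction, the model SE was 0.98-0.99 of the true SD and the size about 5.2-6.2%. The random intercept adds essentially nothing beyond step 2.

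**5. After the change.** REML with an unstructured two-visit covariance held 4.6-5.1% in simulation across the variance ratios. A 6-month analysis of covariance with a t reference, which is equivalent for complete data, held 4.8-5.0%.

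**The case against.** **The certain part is trivial.** An SE 1-2% too small costs about half a percentage point of alpha at most. The upper figure also needs a normal reference that the article does not name, and a degrees-of-freedom method is often left to the full plan. This stands.

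**The covariance part is not shown for the model as listed.** The listed fixed effects have no time-by-condition term, and without it the problem nearly disappears (step 4). This stands for the literal model. But the same section announces between-group effects at both follow-up times, and {18a} makes the first of them primary. The contrast the plan intends is therefore the one exposed.

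**The variance ratio is invented.** The document gives no SD at any visit, so neither the size nor the direction of the error is known. This stands, and it is why the second part is conditional.

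**The 6-month t-tests are unaffected.** True, but they are additional. The mixed model is the analysis named for the primary outcome.

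A reader might infer that the SEs are too small in general and that the test demonstrably misses its 5% level by a wide margin. The document does not support this. Only the maximum-likelihood bias has a fixed direction; the equal-variance constraint can equally make the SE too large. A reader might also add the stratification factors (sex, dialysis type, site) and reach 6.2% at n = 130 or 6.6% at n = 104. Sequence generation {16a} uses those factors to stratify, but {20a} does not put them in the model.

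**Conclusion.** The point holds as a modest specification weakness, not as a demonstrated failure of type I error control.

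- **Certain:** for the listed terms, maximum likelihood makes the SE about 1.2-1.4% too small, and the true size is about 5.3-5.6%.
- **Conditional:** if the model is used for the 6-month contrast and the visit variances differ, the test is mis-sized. For variance ratios of 0.6-0.7 the size is about 8-9%. For 1.3-1.6 it is about 3-4%, with power of about 0.78-0.74 at 130 patients against about 0.81. These ratios are assumptions.
- **Not affected:** a single condition effect pooled over both visits, apart from the small maximum-likelihood bias, and the additional 6-month t-tests.

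A better method costs almost nothing, so the change is worth making even though the harm cannot be sized from the document.

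**What to change.** In {20a}, replace the sentences on estimation and on random effects with wording to this effect: models will be fitted by REML with Kenward-Roger or Satterthwaite degrees of freedom, an unstructured covariance for the 6- and 12-month scores, and fixed effects of baseline score, time, condition and time by condition.

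- The interaction is needed for the model to yield the primary contrast. With time centred at 6 months, the condition coefficient is the 6-month difference.
- Index the covariance by visit (first or second follow-up). Time can then stay continuous in the fixed effects, as the plan wants.
- REML uses all available follow-up data in the same likelihood-based way, so the intention-to-treat argument is unchanged.
- A random slope is not a good substitute: with two roughly fixed follow-up visits it can hardly be separated from residual variance.

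The cost is a few words of analysis text, one extra covariance parameter and slightly wider intervals where maximum likelihood was too narrow. No change to data collection or patient numbers is needed.

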### Interim analyses {21b}

As part of master’s degree education offered at Leiden University, students write their thesis within the context of ongoing research projects and are, for example, involved in the data collection of these projects. We want to offer students the possibility of doing an analysis on the baseline data in a small subsample of participants.

### Methods for additional analyses (e.g., subgroup analyses) {20b}

There are no subgroup analyses planned.

### Methods in analysis to handle protocol non-adherence and any statistical methods to handle missing data {20c}

The primary outcome will be assessed using an intention-to-treat analysis. In addition, we will repeat the analyses with a per protocol analysis using a sample of patients who fully completed the intervention.

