### Trial design {8}

This protocol is a two-arm, parallel-group multicenter randomized controlled superiority trial (RCT), with an allocation ratio of 1:1. Participants will be randomly assigned to one of two groups: (1) the control group that will receive care as usual or (2) the intervention group that will receive 3–4 months of ICBT treatment.

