## Interventions

### Explanation for the choice of comparators {6b}

Participants will be randomly assigned to one of the two groups: (1) the control group that will receive care as usual or (2) the intervention group that will receive 3–4 months of ICBT treatment in addition to usual care. In the Netherlands, usual care for dialysis patients is based on a multidisciplinary approach by a team consisting of nephrologists, dialysis nurses, and specialized social workers that uses complaints and disease-specific PROMS (patient-reported outcome measures) as a base for guidance for medical and psychosocial problems experienced by individual patients. Specialized social workers have to work according to the Dutch Quality Standard for social workers on a dialysis unit. When deemed necessary, additional consultation by a medical psychologist or psychiatrist is routinely available in all Dutch dialysis centers. More information on the Dutch guidelines on renal replacement therapy can be found at https://www.nefrovisie.nl/richtlijnen-indicatoren/.

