### Criteria for discontinuing or modifying allocated interventions {11b}

When a patient’s health significantly worsens over the course of the study, the e-Coach will discuss together with the patient to either discontinue treatment, set the treatment on hold with the possibility to continue in the future, or continue treatment in an adjusted manner (e.g., lower the amount of assignments).

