### Strategies to improve adherence to interventions {11c}

We will regularly ask patients to their needs and wishes in order to optimize the feasibility and the tailored character of the treatment, making the treatment personally relevant for patients. To track adherence, the e-Coach will monitor completed assignments, modules, and the amount of chat messages.

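### The per-protocol repeat is defined by completing an intervention that controls never receive, so it either has no comparison group or is a one-arm selection after randomisation

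*Protocol article*

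**What the plan says.** The section on non-adherence and missing data {20c} has two sentences. The first reads "The primary outcome will be assessed using an intention-to-treat analysis". The second adds that "we will repeat the analyses with a per protocol analysis using a sample of patients who fully completed the intervention".

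The arms differ in exactly the feature that defines this set. Trial design {8} describes "the control group that will receive care as usual"; the section on comparators {6b} describes "the intervention group that will receive 3–4 months of ICBT treatment in addition to usual care".

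On who fails to complete, section {11b} says that if health worsens significantly, patient and e-Coach will decide to "discontinue treatment, set the treatment on hold with the possibility to continue in the future, or continue treatment in an adjusted manner". The limitations part of the Discussion names high disease burden and poor computer skills as drop-out risks. On measuring adherence, section {11c} says that "the e-Coach will monitor completed assignments, modules, and the amount of chat messages", and Table 1 lists e-Coach log data for the intervention group.

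Statistical methods {20a} says that the mixed model "makes use of all available data, making this a full-intention-to-treat analysis". The same paragraph enters the baseline score as a covariate for the effects at post-treatment and follow-up.

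**The concern.** A per-protocol set needs a rule that both arms can meet. Here the rule is completion of ICBT, which exists in one arm only. The analyses to be repeated are the between-condition mixed models of {20a}, and these need controls.

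If all controls are kept and only ICBT completers are compared with them, the groups are no longer those that randomisation formed. Patients who would have stopped ICBT because they were deteriorating leave the intervention side, while their counterparts stay in the control side. A difference can then appear without any treatment effect, and it would be reported next to the intention-to-treat result as though it were the effect of treatment taken as planned.

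The label on the main model raises a smaller, related point. It tells the reader that every randomised patient is analysed, which the stated covariate model does not do.

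**Working it through.** **The plan's own figure.** Sample size {14} gives d = 0.50, alpha .05, 65 per group and power of at least .80. With a two-sided test (sidedness is not stated), 0.50 / √(2/65) = 2.85, and Φ(2.85 − 1.96) = 0.813; the noncentral t gives 0.808. The figure reproduces. It serves here only as the scale for the bias.

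**Literal reading.** Controls able to complete ICBT: 0 of 65. The effect of condition cannot be estimated.

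**Completers against all controls.** Let c be the share of the ICBT arm that completes and g the difference in prognosis between would-be completers and would-be non-completers, in SD units, after baseline adjustment. Randomisation gives both arms the same mixture. With no treatment effect:

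- ICBT completers have mean μ_C.
- All controls have mean c·μ_C + (1 − c)·μ_N.
- The difference is (1 − c)(μ_C − μ_N) = (1 − c)·g.

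The article gives neither c nor g. Assumed ranges are c = 60–80% and g = 0.3–0.5 SD.

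| c | g = 0.3 | g = 0.5 |
|---|---|---|
| 80% | 0.20 × 0.3 = 0.06 | 0.20 × 0.5 = 0.10 |
| 60% | 0.40 × 0.3 = 0.12 | 0.40 × 0.5 = 0.20 |

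Divided by 0.50, this runs from 12% to 40% of the planned effect. At g = 0 it is zero.

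**Cross-check with a second model.** Suppose completion follows a latent normal propensity that correlates ρ with outcome. The spurious benefit is then ρ·φ(z)/c, where z is the normal quantile of c. The last column is the share of 20,000 simulated null trials in which a two-sided 5% t-test against 65 controls rejects.

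| c | ρ = 0.1 to 0.3: benefit (SD) | Rejection rate |
|---|---|---|
| 80% | 0.04–0.11 | 5–9% |
| 70% | 0.05–0.15 | 6–12% |
| 60% | 0.06–0.19 | 6–16% |
| 50% | 0.08–0.24 | 6–20% |

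At ρ = 0 the benefit is 0 and the test rejects in about 5%. The two models agree: at c = 60% and ρ = 0.3 the implied gap is 0.193 / 0.40 = 0.48 SD. The simulation has no baseline covariate, so ρ must be read as what remains after adjustment.

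**The intention-to-treat label.** With baseline on the right-hand side of the model, the outcome rows are the 6- and 12-month scores. A patient with neither score supplies no row. Patients with one score are handled by likelihood, which is valid under missing at random.

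**The case against.** The best defence is that the instruction to repeat the analyses implies that controls stay in, so the empty-control reading is pedantic. A condensed article may also leave the completion threshold and the control rule to the full protocol or SAP. The first part is fair: completers against all controls is the natural reading. But that reading is the one exposed to selection, and no threshold detail would cure it. The undefined threshold is not counted here as a finding in itself.

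Second, a reader might infer that the result is bound to favour ICBT. The documents do not support that. Two of the three options in {11b} keep the door to treatment open, the article describes adapting treatment to prevent drop-out, and the bias vanishes if completion is unrelated to outcome. Adjustment for baseline distress also removes part of any raw gap, so the range above applies only to what remains.

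Third, a reader might infer that this is the trial's only supporting analysis, or that informative drop-out is ignored altogether. Section {20a} also plans t-tests at 6 months. These do not address drop-out, but sensitivity analyses for missing data commonly sit in an SAP, so silence in the article shows nothing.

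Fourth, on the label: {20a} speaks both of change in distress and of baseline as a covariate, so the exact model is not beyond doubt. Under the covariate form that it states, the label claims too much.

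**Conclusion.** The point holds for a supplementary analysis. As worded, the per-protocol repeat either has no comparator or compares a selected part of one arm with the whole of the other. It is open to selection bias, probably towards ICBT given the reasons for stopping that the article itself names. The range of 0.06–0.20 SD rests wholly on the assumed completion rate and residual prognostic gap; the true size cannot be derived from the documents and may be zero.

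Intention-to-treat remains the stated analysis of the primary outcome, so a reader should not conclude that the trial's main result is compromised. The full-intention-to-treat label is a misstatement to correct, not a flaw in the model.

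**What to change.** 1. Replace or supplement the completer analysis with a complier-average causal effect: randomised arm as instrument, the same covariates, and all randomised patients with outcome data. In its simplest form this is the intention-to-treat difference divided by the share p of the ICBT arm that reaches an adherence threshold (controls: 0). If the intention-to-treat effect is zero, so is this estimate.

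2. Fix the threshold from the e-Coach log before outcomes are seen. The estimate assumes no benefit below the threshold. If those below it gain e, the estimate is too high by e·(1 − p)/p. Patients who stop early may already have had the intake, the profile feedback and e-Coach messages, so a low threshold, such as any started module, is safer than full completion. Vary the threshold as a check.

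3. If the completer comparison is kept, state that all controls are included and label it exploratory and non-randomised.

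4. In {20a}, describe the main analysis as covering randomised patients with at least one follow-up score, under missing at random.

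**Cost.** Changes of wording and modest analyst time; adherence is already logged. The interval widens by roughly 1/p relative to intention-to-treat: 1/0.80 = 1.25 to 1/0.60 = 1.67 times at the assumed completion rates, and less with a lower threshold that more patients reach. The report should state both the wider interval and the no-benefit assumption.
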